### Recruitment {15}

In each participating domestic violence shelter, a social worker or therapist who coordinates the flow of incoming and outgoing clients in the shelter is appointed as the contact person for this study. The researcher receives a frequent (weekly or bi-weekly) update of potentially eligible new dyads (mothers with a child aged 0.5–6 years old). In order to perform a more thorough eligibility screening of the dyad, the researcher then contacts the involved social worker for this dyad. This way, we make sure that each dyad with a child in the age range of this study is screened for eligibility for this study and each eligible dyad has the chance to participate. Recruitment of dyads started in December 2020 and will take place until July 2023.

## Assignment of interventions: allocation

### Sequence generation {16a}

In both phases of the RCT, dyads are randomly assigned to one of the two conditions. Randomization occurs with a random number generator in Microsoft Excel (1:1 allocation), stratified by the participating domestic violence shelter locations and using permuted blocks. The first randomization (NIKA versus waitlist CAU) is done prior to the pre-test by a researcher who will not conduct the pre-test. The second randomization (EMDR therapy versus waitlist CAU) is done after post-test 1. Only mothers who report clinical PTSD symptoms on the PCL-5 (for a more detailed description of this questionnaire and the cut-off score that is used, see the “Outcomes {12}” section) are randomized, according to a similar procedure in Microsoft Excel.

### Concealment mechanism {16b}

The first randomization (NIKA versus waitlist CAU) is concealed from the (assistant) researcher who conducts the pre-test, the mother, and the therapist through a closed envelope. For the second randomization (EMDR versus waitlist CAU), concealment is not necessary because the randomization is only performed after the post-test depending on mothers’ self-reported PTSD symptoms.

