### Implementation {16c}

The first randomization (NIKA versus waitlist CAU) is performed prior to the pre-test by a researcher who will not conduct the pre-test with the dyad. The (assistant) researcher who conducts the pre-test is unaware of the condition the dyad is in and brings a closed envelope to the pre-test. This (assistant) researcher opens the envelope with the mother at the end of the pre-test and then informs the involved therapist. The second randomization (EMDR versus waitlist CAU) occurs after the first post-test by one of the researchers. The mother and therapist are informed about the condition once the researcher has performed this randomization sequence as described above.

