## Data collection and management

### Plans for assessment and collection of outcomes {18a}

At all three time points, the mother-child dyad is invited for a 1-h research appointment. All research appointments are similar in structure and content. After a short explanation of the (assistant-)researcher, the mother is asked to fill out a general questionnaire (only during the pre-test), the BSI [73], and CATS [70]. Then, a 10-min free play observation is conducted and videotaped. During the first 5 min of this observation, the mother and child are instructed to play together without toys as they would normally do. Next, a set of toys is provided, and the mother and child are instructed to play with these toys as they would normally do. The set of toys consists of a too large variety of toys, including a hand puppet, a toy that can make much noise, and age-inappropriate toys. Also, ambiguous toys (such as a spider and a police car) are included. After 4 min, the mother is instructed to clean up the toys with her child. These elements were included to make the play session a bit more challenging and stressful for the mothers. After the observation task, the mother is asked to fill out the CTQ [75], LEC-5 [60], PCL-5 [60], and CBCL [72]. All questionnaires are filled out on a laptop using the survey platform Qualtrics, or, in case this has the mother’s preference, on paper. The researcher remains in the same room during the administration of the questionnaires, so that the mother can ask questions. Because some questionnaires may elicit negative emotions in the mothers, the researcher remains vigilant of any signs of distress in the mother while she is filling out the questionnaires. If this occurs, the researcher will comfort the mother and pause the research appointment as long as necessary. At the end of the research appointment, the researcher will point the mother towards the possibility to contact her social worker if she would like to talk about anything related to the questionnaires. Even though the child is present during the observation talk, whenever possible the child will not be in the same room while the mother fills out the questionnaires. In most domestic violence shelters, there is an internal child care facility where the child can stay during this time. If this is not an option, the second researcher who is present will watch the child in another room while the mother fills out the questionnaires.

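### The second randomisation is wrongly said to need no concealment, which leaves a limited, avoidable exposure to selection bias in the EMDR comparison

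*Protocol article*

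**What the plan says.** Concealment mechanism {16b} treats the two randomisations differently. The first "is concealed from the (assistant) researcher who conducts the pre-test, the mother, and the therapist through a closed envelope". For the second, "concealment is not necessary because the randomization is only performed after the post-test".

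Sequence generation {16a} describes 1:1 allocation from Excel random numbers, "stratified by the participating domestic violence shelter locations and using permuted blocks". It adds that mothers with clinical PTSD symptoms "are randomized, according to a similar procedure in Microsoft Excel". Block size is not given.

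Implementation {16c} separates roles in phase 1: the first randomisation "is performed prior to the pre-test by a researcher who will not conduct the pre-test with the dyad". For phase 2 it says only this: "The second randomization (EMDR versus waitlist CAU) occurs after the first post-test by one of the researchers". Mother and therapist learn the result afterwards.

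Entry to phase 2 depends on a PCL-5 total of 31 or more at the first post-test (Intervention description {11a}, EMDR therapy). On how the questionnaires are completed, Plans for assessment and collection of outcomes {18a} states: "The researcher remains in the same room during the administration of the questionnaires, so that the mother can ask questions". Under Who will be blinded {17a}, mothers, therapists and social workers know the condition, and assessors need not be blinded.

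**The concern.** Allocation concealment means that nobody who can influence a participant's entry knows, or can work out, the next assignment before entry is settled. The time of the draw does not secure this. A list may already exist, and in a blocked sequence earlier allocations partly fix later ones.

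The EMDR comparison tests the second primary hypothesis. Its entry score is also its baseline, because the analysed change runs from the first to the second post-test (Outcomes {12}). If a researcher who expects a particular arm influences a total close to 31, two things change: who is compared, and the starting value from which change is measured. Intention-to-treat analysis and multiple imputation act after randomisation and cannot repair selective entry.

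**Working it through.** **The plan's own figure.** The plan gives no figure for predictability. Its phase 2 power of 75% (n = 40 per group, d = 0.60, two-sided α = .05) is consistent with a simple two-group check, which is not a re-run of the three-level model. The noncentrality is d·√(n/2) = 0.60 × √20 = 2.68. The normal approximation gives Φ(2.68 − 1.96) = 76.5%, and the noncentral t with 78 degrees of freedom gives 75.5%. Concealment does not alter this figure.

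**The two randomisations side by side.**

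| Feature | First (NIKA) | Second (EMDR) |
|---|---|---|
| Sequence | Excel, 1:1, blocks within location | Similar Excel procedure |
| Timing of draw | Before the pre-test | After the first post-test |
| Concealment | Closed envelope | Declared unnecessary |
| Randomiser separate from assessor | Required | Not stated |
| Entry rule | Eligibility criteria and consent | PCL-5 of 31 or more |

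The later draw removes one risk: no result for that dyad has to be hidden while she is assessed. It leaves two others, namely sight of the list and inference from earlier allocations.

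**How predictable the sequence could be.** Assumptions, none of them stated in the protocol: the block size is fixed at 2m and known; all earlier phase 2 allocations at the location are known in order; blocks are completed.

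- Share of allocations fully determined by earlier ones: 1/(m + 1).
- Expected share guessed correctly, always naming the arm with more places left: [m + 2^(2m−1)/C(2m, m) − ½] / (2m).

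| Block size | Determined | Best guess correct |
|---|---|---|
| 2 (m = 1) | 1/2 = 50% | (1 + 2/2 − 0.5)/2 = 75% |
| 4 (m = 2) | 1/3 = 33% | (2 + 8/6 − 0.5)/4 = 71% |
| 6 (m = 3) | 1/4 = 25% | (3 + 32/20 − 0.5)/6 = 68% |

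Full enumeration of the blocks gives the same values. Without any knowledge, a guess is right 50% of the time. For the planned 80 mothers, the determined allocations would number 40, about 27 (80/3) or 20. These are upper limits: determined places fall at the end of a block, so unfinished blocks at a location lower the share.

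**From prediction to bias.** Predictability matters only where entry can still be influenced, chiefly for totals near 31. The documents do not say how many mothers score there, so no size of bias can be calculated.

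**The case against.** The strongest defence is that phase 1 needs an envelope because the result exists before the assessment, whereas in phase 2 nothing is described as drawn until the assessment is over. There is also little discretion. The mother consented before the pre-test, and entry is a fixed cut-off on her own answers, not a clinical judgement. Participant timeline {13} starts phase 2 in the week of the first post-test, which limits delay. Plans to promote participant retention {18b} commits the team to finishing incomplete assessments, which limits selective chasing of unfinished forms. The interpreter is an outside professional on a speaker, and nothing suggests knowledge of the sequence.

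Most of this stands, and it shrinks the exposure. It does not rescue the stated reason, because none of it hides a blocked sequence from a researcher who may both run the assessment and make the draw.

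A reader might go further and infer that the EMDR comparison is biased, or that assessors know the next allocation. The documents support neither. They do not say who can see the Excel list, whether block sizes vary, or whether any assessor follows a location's sequence. A reader might also count the unblinded self-reported outcome as making this worse. That is a separate measurement issue, which concealment would not change.

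**Conclusion.** The statement in {16b} is wrong as a reason, and the missing separation of roles in {16c} leaves the second randomisation less protected than the first. The result is a possible and limited exposure to selection bias in a primary comparison, concentrated among mothers scoring near 31 who complete the form with a researcher present. Determined shares of 50%, 33% or 25%, and correct guesses of 75%, 71% or 68%, are worst-case values for assumed block sizes of 2, 4 or 6. They measure predictability and do not estimate bias.

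The finding assumes that the similar procedure in phase 2 keeps the blocks within location, as the section's description of both phases indicates. The point should be fixed, because concealment cannot be restored at analysis. It does not by itself invalidate the comparison.

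**What to change.** For the randomisations still to come:

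1. Delete the statement that concealment is unnecessary.
2. Have a researcher who does not conduct that dyad's first post-test hold the concealed sequence, as in phase 1.
3. Record and lock the PCL-5 total and the eligibility decision (a Qualtrics time stamp or a signed paper score) before the allocation is released.
4. If block sizes are fixed, vary them, and keep them from assessors.

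The envelopes and the separate researcher already exist for phase 1, so the practical cost is a short extra step between scoring and allocation. Recruitment had begun when the article was written, and important modifications need approval from the ethics committee, so an amendment is also required. The change cannot protect mothers already allocated.

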### Implementation {16c}

The first randomization (NIKA versus waitlist CAU) is performed prior to the pre-test by a researcher who will not conduct the pre-test with the dyad. The (assistant) researcher who conducts the pre-test is unaware of the condition the dyad is in and brings a closed envelope to the pre-test. This (assistant) researcher opens the envelope with the mother at the end of the pre-test and then informs the involved therapist. The second randomization (EMDR versus waitlist CAU) occurs after the first post-test by one of the researchers. The mother and therapist are informed about the condition once the researcher has performed this randomization sequence as described above.

## Assignment of interventions: blinding

### Who will be blinded {17a}

Participating mothers and their therapists and social workers cannot be blinded for study condition in this trial, because the control group is placed on a waitlist. The research assessments only include self-report questionnaires (in the presence of a researcher) and a video observation with no interference from the researcher. Therefore, it is not necessary to blind the researchers who perform the assessments to the study condition of the dyad. All observational data in this study will be coded by researchers who are blind to the condition of the dyads.

### Procedure for unblinding if needed {17b}

A procedure for unblinding is not needed in this study, because the participants and involved social workers and therapists are aware of the condition the dyad is in.

## Data collection and management

### Plans for assessment and collection of outcomes {18a}

At all three time points, the mother-child dyad is invited for a 1-h research appointment. All research appointments are similar in structure and content. After a short explanation of the (assistant-)researcher, the mother is asked to fill out a general questionnaire (only during the pre-test), the BSI [73], and CATS [70]. Then, a 10-min free play observation is conducted and videotaped. During the first 5 min of this observation, the mother and child are instructed to play together without toys as they would normally do. Next, a set of toys is provided, and the mother and child are instructed to play with these toys as they would normally do. The set of toys consists of a too large variety of toys, including a hand puppet, a toy that can make much noise, and age-inappropriate toys. Also, ambiguous toys (such as a spider and a police car) are included. After 4 min, the mother is instructed to clean up the toys with her child. These elements were included to make the play session a bit more challenging and stressful for the mothers. After the observation task, the mother is asked to fill out the CTQ [75], LEC-5 [60], PCL-5 [60], and CBCL [72]. All questionnaires are filled out on a laptop using the survey platform Qualtrics, or, in case this has the mother’s preference, on paper. The researcher remains in the same room during the administration of the questionnaires, so that the mother can ask questions. Because some questionnaires may elicit negative emotions in the mothers, the researcher remains vigilant of any signs of distress in the mother while she is filling out the questionnaires. If this occurs, the researcher will comfort the mother and pause the research appointment as long as necessary. At the end of the research appointment, the researcher will point the mother towards the possibility to contact her social worker if she would like to talk about anything related to the questionnaires. Even though the child is present during the observation talk, whenever possible the child will not be in the same room while the mother fills out the questionnaires. In most domestic violence shelters, there is an internal child care facility where the child can stay during this time. If this is not an option, the second researcher who is present will watch the child in another room while the mother fills out the questionnaires.

In case the mother does not (sufficiently) speaks Dutch or English, a professional interpreter will be called and put on a speaker to guide the mother through the research appointment. Furthermore, all research information has been translated into English and Arabic for this study, because we expected these two languages would be the most prevalent among non-Dutch-speaking mothers. Whenever possible, validated international versions of the questionnaires are used in the language of the mother. For the CTQ [75], CATS [70], and BSI [73], no validated Arabic version was available. We translated these questionnaires for this study through a back-and-forth translation method by a native Arabic speaker and a professional Arabic translator. In case the mother has a different native language than Dutch, English, or Arabic, or the mother is analphabetic, the interpreter will provide live translations of the questionnaires to the mother during the appointment.

*Disrupted parenting behavior* is assessed at all time points based on the 10-min observation of mother-child interactions. We will use the AMBIANCE [63] to code disrupted parenting behavior. Coders will be trained through the standard AMBIANCE training and should achieve a satisfactory intraclass correlation coefficient (ICC) for the overall level of disrupted communication on a subset of videotapes from both observational tasks in this study (ICC ≥.70). In addition, regular supervision sessions will be organized throughout the coding process to prevent coder drift.

*Parental sensitivity* is assessed at all time points using the same observations as described above. We will use the Ainsworth scale for sensitivity [64]. Coders will be trained by an experienced researcher who has been previously trained in the Ainsworth scale. Similar to the AMBIANCE, coders should achieve satisfactory intraclass correlation coefficient (ICC) rates for the sensitivity scale on a subset of videotapes of this study (ICC ≥.70) and regular supervision sessions will be organized throughout the coding process.

All questionnaires that are used in this study are well-validated instruments, see the “Outcomes {12}” section for more details.

### Plans to promote participant retention and complete follow-up {18b}

We stimulate the participating dyads to complete all study assessments in several ways. We provide the mothers with a small compensation of €20, after each assessment, and the child with a small gift (age-appropriate toys). After the final research appointment, we send the mothers a compilation of the videotaped mother-child interactions through a secured link. Throughout each dyad’s research trajectory, we aim to be as flexible as possible to fit the research appointments in their schedule. If not all parts of the research appointment can be completed in one appointment, we schedule another appointment as soon as possible to finish all remaining assessments. If the dyad moves away from the domestic violence shelter during the study, we will visit the dyad in their new home for the upcoming research appointments. In the analyses, we will account for potential missing data by applying multilevel multiple imputation.

### Data management {19}

All questionnaires are collected digitally through Qualtrics. Questionnaires that are filled out on paper by the mother are entered into Qualtrics by a research assistant. During data collection, Qualtrics data are copied to an SPSS file on a weekly basis (each new version of the SPSS file is saved under a new name, including the current date). Digital data (including questionnaires, videotapes, databases, and processed data) are stored in a secured folder within the university network that is only accessible to research members and has automated back-ups. Questionnaires and videotapes that have to be shared with the NIKA or EMDR therapists for the treatment sessions never contain the names of the participants and are shared through a secured link (SURFdrive). The dyads each get an identification code, which is not based on their initials or birth date, and a subject identification list is used to link these numbers to the participants. Video recordings of therapy sessions and all therapy documents (e.g., intake and session forms) are transported to the research team by the therapists through a secured link. These data will be stored in a secured folder that can only be accessed by the researchers. The handling of the personal data complies with the EU General Data Protection Regulation and the Dutch Act on Implementation of the General Data Protection Regulation (Uitvoeringswet AVG, UAVG). Informed consent by the parent(s) is obtained to save the research data for future research. With the consent of the parent(s), all data will be stored for 10 years. All data handling and storage procedures are also extensively described in a data management plan in DMPonline.

### Confidentiality {27}

All research data are pseudonymized and stored in closed facilities within Leiden University as described under the “Data management {19}” section and are only accessible by members of the research team. The conversion key and all participant information (e.g., contact details) are stored separately from the research data in an encrypted file.

### Plans for collection, laboratory evaluation, and storage of biological specimens for genetic or molecular analysis in this trial/future use {33}

Not applicable, we do not collect biological specimens.

## Statistical methods

### Statistical methods for primary and secondary outcomes {20a}

We will conduct the analyses for this study through three-level linear mixed effect models in R (nlme, lmr, and mitml packages) that account for repeated measures over time (level 1) and nesting of dyads (level 2) within therapists (level 3). More details on the analyses are described earlier in this protocol under the “Outcomes {12}” and “Sample size {14}” sections.

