## Interventions

### Explanation for the choice of comparators {6b}

All dyads receive care as usual (CAU) in the domestic violence shelter. The comparison group in this study is placed on a waitlist for NIKA and, if applicable, EMDR. The main reason for this choice is that it would be unethical to withhold the participating dyads completely from these interventions. In addition, the domestic violence shelter already offers an environment in which families receive support to deal with the consequences of domestic violence. Mothers and their children usually reside in the domestic violence shelter for a period of 6 weeks to 9 months, depending on the domestic violence shelter organization and the possibilities for transitioning to permanent housing. After this period, further treatment is continued through ambulatory care. The goal of the guidance that is provided to women in the domestic violence shelter is to develop a safe environment and to learn how to become independent and how to prevent becoming involved in interparental violence again in the future. The standard guidance that is provided in the different domestic violence shelters is roughly similar: a social worker is involved with the family throughout their stay in the domestic violence shelter. This social worker also involves the social network, and, if possible, the non-residing parent in the treatment plan for the family. In addition, help is provided to mothers with respect to practical issues such as financial problems, schooling for the child and mother, legal issues, and future housing of the family. In addition to individual support, group activities (e.g., support groups for mothers) are regularly organized. Even though the participating domestic violence shelter organizations have slightly different emphases, both organizations use nationally available protocols for support in domestic violence shelters [56, 57]. Currently, these protocols do not include an assessment of the need to provide trauma- and attachment-based interventions nor routine offering of such intervention. If the mothers or children need more specialized support, this is provided by either an external youth care organization or by psychologists from the domestic violence shelter.

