### Sample size {14}

The planned sample size for this study is *N* = 150. Separate power calculations for the two study phases have been conducted.

#### Phase 1

We conducted a power analysis for longitudinal linear mixed effect models with unbalanced designs in R using the “powerlmm” package [76]. Based on recent meta-analyses regarding the effectiveness of trauma-informed parenting interventions after violence exposure [77] and a short-term attachment-based intervention that includes some components similar to NIKA [78], we assumed an effect size of *d* = 0.50 for the effects of NIKA on disrupted and sensitive parenting. We estimated three-level models accounting for repeated measures over time (level 1) and partial nesting of families (level 2) within therapists (level 3) (only in the NIKA group). We estimated approximately 50% variance to occur between subjects and 5% variance between therapists. For a sample of *N* = 150 (*n* = 75 per group), two time points, and two-sided testing with a significance level of *α* = .05, we will have 86% power to detect effects of *d* = 0.50.

#### Phase 2

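### Randomization is stratified by shelter location but no stated model contains shelter, so the standard error of the condition effect may be slightly too large

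*Protocol article*

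**What the plan says.** Sequence generation {16a} covers both randomizations: "In both phases of the RCT, dyads are randomly assigned to one of the two conditions". It continues: "Randomization occurs with a random number generator in Microsoft Excel (1:1 allocation), stratified by the participating domestic violence shelter locations and using permuted blocks". For phase 2, mothers above the PCL-5 cut-off "are randomized, according to a similar procedure in Microsoft Excel".

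Statistical methods {20a} describes three-level linear mixed models that "account for repeated measures over time (level 1) and nesting of dyads (level 2) within therapists (level 3". It then sends the reader elsewhere in the same article: "More details on the analyses are described earlier in this protocol under the “Outcomes {12}” and “Sample size {14}” sections". Outcomes {12} defines each comparison as a difference between conditions in change between two assessments. Sample size {14} uses, for phase 1, "partial nesting of families (level 2) within therapists (level 3) (only in the NIKA group"; for phase 2, the third level is the previous condition. The additional analysis {20b} of NIKA plus EMDR against NIKA alone has two levels, repeated measures within dyads. None of these places names shelter as a covariate, stratum or level. Outcomes {12} says only that shelter characteristics will be documented.

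On whether shelters differ, Explanation for the choice of comparators {6b} points both ways. It begins one sentence with "Even though the participating domestic violence shelter organizations have slightly different emphases", and it says that length of stay (6 weeks to 9 months) depends partly on the organization. It also calls the standard guidance roughly similar and says that both organizations use nationally available protocols.

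**The concern.** Permuted blocks within location balance the arms on shelter. Where shelter is related to the outcome, that balance lowers the true variance of the treatment contrast. A model without shelter does not recognise this: it leaves the between-shelter variation in the residual and reports a standard error that is too large.

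No other stated level takes over the role of shelter. Therapist nesting is applied only in the NIKA group, so waitlist dyads have no term that could carry shelter differences. The third level in the phase 2 power model is the previous condition, and the combined-effect model has no third level.

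At stake is some efficiency, most usefully in phase 2, where planned power is only 75%. There is also the risk that the choice between adjusted and unadjusted results is made after the data are seen.

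**Working it through.** **Inputs from Sample size {14}.** Phase 1: d = 0.50, 75 per group, 50% of variance between subjects, two time points, two-sided α = .05, stated power 86%. Phase 2: d = 0.60, 40 per group, same variance share and α, stated power 75%.

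**Assumed, because the article gives none.** The share f of the variance in change that lies between shelters, the number of locations, and the block size.

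**1. The stated power, without any shelter term.** With 50% between-subject variance, the SD of change is √(2 × (1 − 0.50)) = 1.0.
- Phase 1: SE = √(2/75) = 0.163; 0.50/0.163 = 3.06; power Φ(3.06 − 1.96) = 86.5% by the normal approximation, 86.0% by noncentral t (stated 86%).
- Phase 2: SE = √(2/40) = 0.224; 0.60/0.224 = 2.68; power 76.5% and 75.5% respectively (stated 75%).

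The planned figures reproduce and do not depend on a shelter term.

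**2. Shelters that differ only in level.** A constant shelter effect enters pre-test and post-test alike and drops out of the change. Simulation (3,000 runs per setting, blocks of 4 within 4 or 10 locations, change-score analysis, shelter level variance 0–10% of the variance at one time point) gave a phase 1 SE of 0.163 and power of 85–86% with or without shelter. Phase 2 power was 74–75% either way.

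**3. Shelters that differ in change: closed form.** With exact balance within locations, the true variance of the contrast is (1 − f)V, while the unadjusted model reports V.
- Unadjusted type I error = 2Φ(−1.96/√(1 − f)): 4.4% at f = 0.05 and 3.9% at f = 0.10.
- For phase 1, 86% power corresponds to a standardised effect of 1.08 + 1.96 = 3.04. Unadjusted power = Φ(1.08/√(1 − f)); adjusted power = Φ(3.04/√(1 − f) − 1.96).

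| f | Unadjusted | Adjusted | Gain |
|---|---|---|---|
| 0.05 | 86.6% | 87.7% | 1.1 points |
| 0.10 | 87.3% | 89.3% | about 2 points |

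Unadjusted power already exceeds 86% here, because the stratified design has reduced the true variance. The gain from adjustment must be counted from these values and not from 86%.

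**4. Shelters that differ in change: simulation.** Same set-up, with a shelter-by-time variance of 0.10 against a change variance of 1:
- Phase 1: mean model SE 0.161–0.162 unadjusted and 0.155 adjusted. The actual SD of the estimate was 0.154–0.156, so the unadjusted SE is about 4–5% too large. Power rose from 87.2% to 88.9% (4 locations) and from 88.0% to 89.9% (10 locations).
- Phase 2: power rose from 76.8% to 78.7% and from 78.1% to 80.0%, about 2 points.
- Unadjusted type I error was 4.1–4.6% across both phases.

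At a variance of 0.05, the gain was 0.5–0.8 points in phase 1 and about 1 point in phase 2.

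For phase 2 at f = 0.10 the closed form gives a little more: Φ(0.6745/√0.9) = 76.1% against Φ(2.6345/√0.9 − 1.96) = 79.3%, about 3 points. It assumes exact balance and no loss of degrees of freedom. In the simulation, blocks can be incomplete, and the share realised among K drawn locations averages only 0.10 × (K − 1)/K, that is 0.075 for 4 and 0.09 for 10. The simulated 2 points is the more realistic figure.

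**The case against.** The strongest reply is that the sentence in {20a} lists nesting levels and is not a list of covariates: it names no fixed effects at all, not even condition or time. A journal article often leaves stratification covariates to a full protocol or analysis plan, and none is shown here. That an unseen document may add shelter is granted. What remains is that the article states a model structure, refers only to its own sections for detail, and names shelter in none of them. As published, the analysis does not follow the randomization.

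The second reply is that shelter may hardly matter. The article calls the guidance roughly similar, nothing in it gives the size of any shelter effect on change, and differences in level cancel. This stands, and it is why the size is given as conditional on an assumed share, with zero as the lower end.

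The third is that the fix has a price: the number of locations is not stated, so the degrees of freedom it uses are unknown, and the combined-effect comparison is small. This also stands and shapes the fix.

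A reader might infer more than the article supports, in three ways:
- That the stated power is wrong. It reproduces without shelter.
- That the primary tests are invalid. Omission makes them slightly conservative.
- That the therapist term in the NIKA arm absorbs shelter differences and so distorts the comparison. This would need therapists to be aligned with shelters. The article does not say so, and Study setting {9} says that therapists travel to the locations.

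**Conclusion.** The mismatch is real and its consequence is small. Shelter location stratifies the first randomization explicitly and the second by a similar procedure, yet it appears in no stated model. If shelters differ only in level, nothing is lost. If they explain 5–10% of the variance in change, the unadjusted type I error is roughly 4–4.5% (3.9% in the limiting case of exact balance at 10%), and adjustment adds about 1–2 points of power in phase 1 and about 2 points in phase 2 at 10%.

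These sizes rest on the assumed shelter share, on 4 or 10 locations with blocks of 4, and on a change-score analysis without a therapist level. There is no bias and no excess of false positives, and no primary conclusion is threatened. It is still worth correcting, because the variable is already recorded and the choice is best fixed before the data are seen.

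**What to change.** Include shelter location in the phase 1 and phase 2 models for primary and secondary outcomes, in one of two forms:
- as a covariate, if the post-test is modelled with adjustment for the preceding assessment; or
- as location plus location-by-time, if the repeated-measures form is kept. A location intercept alone would cancel from the change and achieve nothing.

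If there are many small locations, use random effects or pool them by organization under a rule set in advance. In the small comparison of NIKA plus EMDR with NIKA alone, use the pooled or random term only. If shelter is to be left out, say so and give the reason.

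No new data are needed. The cost is some degrees of freedom, how many depending on the number of locations, which the article does not state. This weighs more in phase 2 (80 mothers planned) and most in the combined-effect comparison.
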